### Randomization and blinding

2.6

Participants will be randomly allocated to the 2 groups through a sequence of numbers generated by a computer program before starting the selection process. The group assigned to each patient will be kept in a sealed envelope with the objective of concealing the assignment to the researcher, who will decide on the entry of subjects to the study. Given the nature of the interventions, the physiotherapists, and the patients, blinding will not be possible. However, the evaluator and statistician will be blinded to which group the subjects evaluated will belong.

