**Methods/design::**

In this study, we will use our own front-to-back clinical research method. We plan to include 120 young and middle-aged female patients who meet the diagnostic criteria for pathological scars. The untreated pathological scars of the enrolled patients will be used as blank controls. The intervention group will be given conventional western medicine treatment and combined Chinese and western medicine treatment. The assessment of scar area, color, hardness, thickness, itching, and pain was recorded for 8 weeks of treatment.

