#### Inclusion criteria

2.2.2

This study will be conducted in China. Patients will be recruited from Plastic surgery departments of the Second Affiliated Hospital of Shaanxi University of Chinese Medicine. We will enroll participants based on the following inclusion criteria:

1.It meets the diagnostic criteria for pathological scars;2.There are at least 3 pathological healing scars throughout the body.3.Female patients of 16 ≤ age ≤ 40 years old;4.The time for the formation of fatigue marks exceeds 3 months;5.Those who have voluntarily signed the informed consent.

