### Interventions

2.3

The participants included in the observation will be self-controlled, and each patient randomly selected 3 different scar treatment areas at the same site as observation specimens.

Control group: Take the untreated pathological scars of the participants as blank control. This group will not give any intervention.

Intervention group: Among the two pathological scars, group A will be treated with conventional external medicine of western medicine, and group B will be treated with oral TCM decoction combined with conventional external medicine of western medicine. The main components of the TCM prescription are: *Baizhi, Jiazhu, Leiwan, Maidong, Yuanhu, Taoren, Honghua*, and *Jingjie*. Specific treatment method: clean the scar area, apply gel to the affected area, every 3 times. TCM decoction is taken orally after meals, 3 times a day. The total application time will be 8 weeks. At the same time, closely monitor the change of the condition in order to control the deterioration of the condition in time (Fig. 2).

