### Sample size calculation

2.5

The sample size for this trial is based on an expected mean difference between groups of 11 points of the Constant–Murley questionnaire, which is the minimum clinically important difference. To detect this difference between both treatments, with a value of *a* = 0.05 (probability of committing a type I error) and a statistical power of 95%, a minimum of 49 patients per group is needed. This minimal sample size estimate has been increased by 20% after considering the potential dropouts, finally including 60 patients for each group. Accordingly, the proposed experimental hypothesis is that there will be a difference of at least 11 points in the Constant–Murley questionnaire in the intervention group versus the control group. The sample size was determined using the Stata SE software, version 15.

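### Randomisation assigns each patient to one of two groups, but the interventions put blank, A and B on three scars of the same patient; no random allocation of scars to conditions is described

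*Protocol article*

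**What the plan says.** Two designs stand in the protocol article.

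- **Patients in two groups.** Section 2.6: "Participants will be randomly allocated to the 2 groups through a sequence of numbers generated by a computer program", and then "The group assigned to each patient will be kept in a sealed envelope". Section 2.5 asks for at least 49 patients per group, raised to 60. This agrees with the abstract's total: "We plan to include 120 young and middle-aged female patients".
- **Scars within a patient.** Section 2.3 calls participants self-controlled and says that "each patient randomly selected 3 different scar treatment areas at the same site as observation specimens". For the control it says: "Take the untreated pathological scars of the participants as blank control". For the rest: "Among the two pathological scars, group A will be treated with conventional external medicine of western medicine", with group B given an oral decoction on top of the same external medicine. The abstract also uses the patients' own untreated scars as blank controls.

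Eligibility in section 2.2.2 supports the second design: "There are at least 3 pathological healing scars throughout the body". No section says how a given scar comes to be blank, A or B.

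**The concern.** The unit that is randomised and concealed (the patient) is not the unit to which section 2.3 gives the conditions (the scar). The number of groups differs too: two in sections 2.5 and 2.6, three conditions in section 2.3.

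At stake is the comparison of treated with untreated scars. If someone may decide which scar to leave untreated, severity can guide the decision. The efficacy index in section 2.4.1 is the change in score divided by the score before treatment, so it is sensitive to scars that start at different levels. Section 2.6 says that patients and treating staff cannot be blinded, so allocation is the main safeguard. The blinded evaluator does not replace it: regression to the mean arises even when every score is read without bias.

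The two designs also need different analyses. A between-patient contrast and a within-patient contrast have different variances, so neither the sample size nor the tests can be judged until one design is fixed.

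**Working it through.** **1. The plan's own figure.** Inputs from section 2.5: difference 11 points, type I error 0.05, power 95%, 49 per group, 20% for dropout, 60 per group. No SD and no sidedness are given, so 49 cannot be confirmed directly. For two independent means, n per group = 2 × (z_alpha + z_power)² × SD² / difference². Solved for the SD:

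- two-sided: 11 × √(49/2) / (1.960 + 1.645) = 11 × 4.950 / 3.605 = 15.1 points
- one-sided: 11 × 4.950 / (1.645 + 1.645) = 16.6 points

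For an assumed SD of 10 to 20, the two-sided n runs from 22 to 86 per group. For dropout, 49 × 1.2 = 58.8 (59) and 49 / 0.8 = 61.25 (62); the stated 60 lies between them. Twice 60 is the 120 of the abstract. The figure therefore fits a two-sample layout at a suitable SD. That alone proves little, because the SD is free. It is the wording, patients per group with two groups, that fixes the layout as parallel.

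**2. The sections side by side.**

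- Unit: patient (2.5, 2.6) against scar within patient (2.3, abstract).
- Number of arms: two (2.5, 2.6) against three conditions (2.3).
- What is concealed: one group per patient (2.6). Nothing is said of a code for scars.
- Use of chance at scar level: three areas are picked at random to be observed (2.3). That samples scars. It does not say which of the three receives which condition.

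**3. Can the envelope do the job?** Three conditions can be placed on three scars in 3! = 6 ways. A two-group code distinguishes 2. It cannot carry the assignment that section 2.3 needs.

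**4. Size of the exposure (illustration, assumed values).** Assume that the observed scores of three scars in one patient are normal with SD 2 to 3 points, that score reliability is 0.7, and that the mildest-looking scar is left untreated. The scale in section 2.4.1 has six items of up to 3 points, so a maximum of 18.

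- Expected ordered values of three normals: −0.846, 0 and +0.846 SD.
- Mean of the two treated scars: (0 + 0.846) / 2 = 0.423 SD.
- Gap to the blank scar: 0.423 + 0.846 = 1.269 SD.
- Spurious difference in change: (1 − 0.7) × 1.269 × SD = 0.381 × SD.
- SD 2: 0.76 points. SD 3: 1.14 points.

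The figure is proportional to the SD and to one minus the reliability. It is zero if the choice of scar is unrelated to severity.

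**5. Eligibility.** Section 2.2.2 counts scars anywhere on the body, while section 2.3 takes three areas at one site. A patient with three scattered scars is eligible but does not fit the intervention as described.

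**The case against.** Several stronger readings are tempting, and the document does not support them.

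- **That the untreated scar is known not to be randomised.** The article is silent on how it is chosen. What can be said is that no random allocation of scars is described and that the scheme which is described acts on another unit. That the mildest scar would be left alone is conjecture, used above only to size the exposure.
- **That the concealment in section 2.6 protects nothing.** Patients may be randomised to A or B, each keeping an untreated scar. Section 2.5 does speak of a difference between two treatments. On that reading the sealed envelope protects A versus B, and only treated versus blank is exposed. The reading sits badly with section 2.3, which places A and B among two scars, but it cannot be ruled out.
- **That the bias is 1.0 to 1.5 points.** This follows from comparing the worst scar with the mildest (1.69 SD). If the mildest is left untreated, the treated scars are the other two, and the gap is 1.27 SD.
- **That the bias nearly equals what the trial can detect.** A benchmark from 49 per group is unpaired and does not fit a within-patient contrast, so no such comparison is made here. Nor is the illustration carried over to the percentage index in section 2.4.1. Scars at the same site may also vary less than assumed.

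It may also be said that an article condenses the full protocol. That would excuse a missing detail. It does not excuse sections that state incompatible designs, because no fuller document can make all of them true.

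**Conclusion.** The contradiction stands on the text and needs no assumption: sections 2.5 and 2.6 allocate patients to two groups, section 2.3 and the abstract put three conditions on the scars of each patient, and one two-way code per patient cannot serve both. As written, treated versus blank has no described protection against selection of scars by severity. A versus B is protected only if patients are in fact randomised between them.

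The size, 0.76 to 1.14 points for the average of two treated scars against the blank, is an illustration. It rests on the assumed SD, the assumed reliability and the assumed choice of the mildest scar, none of which is in the article. The mismatch over the site of the scars is a separate, minor point of eligibility.

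This should be settled before enrolment. Section 2.9 says that recruitment has not started, and allocation cannot be repaired afterwards.

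**What to change.** State one unit of allocation and one number of groups in sections 2.3, 2.5 and 2.6:

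- Randomise patients to A or B from the computer list.
- Number each patient's scars in advance. Let the same sealed envelope carry a random code for the scar that stays without external treatment, and open it only after all scars have been scored at baseline.
- Analyse A versus B between patients, and treated versus untreated scar within patients.

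Do not randomise three scars of one patient to blank, A and B. The decoction in B is oral and reaches every scar of the patient who takes it, so B could not be separated from A or from blank. For the same reason, the untreated scar of a B patient is a control for the external treatment only. The statement in section 2.3 that the control receives no intervention must be reconciled with this.

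Also reconcile the eligibility rule in section 2.2.2 (scars anywhere on the body) with the same-site areas in section 2.3.

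Cost: a longer randomisation list, and matching edits to the sample size (section 2.5) and the analysis (section 2.7). No extra visits or staff are needed. If the same-site rule is kept, recruitment may be slightly slower.

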### Outcome measures

2.4

The assessment of scar area, color, hardness, thickness, itching, and pain was recorded for 8 weeks of treatment. Assess fatigue marks once a week and save case photos.

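### The evaluator's mask is stated by subject, but in the self-controlled design the conditions differ by scar, so the mask as worded does not conceal which scar is treated

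*Protocol article*

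**What the plan says.** **Unit that carries the conditions.** Section 2.3 (Interventions) states: "The participants included in the observation will be self-controlled, and each patient randomly selected 3 different scar treatment areas at the same site". For the control it says: "Take the untreated pathological scars of the participants as blank control". For the active conditions it says: "Among the two pathological scars, group A will be treated with conventional external medicine of western medicine". Group B is the scar given an oral decoction together with the external medicine. The abstract agrees: "The untreated pathological scars of the enrolled patients will be used as blank controls". So does the inclusion criterion: "There are at least 3 pathological healing scars throughout the body".

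**Unit that is masked.** Section 2.6 (Randomization and blinding) states that "the evaluator and statistician will be blinded to which group the subjects evaluated will belong". The same section says that patients and treating staff cannot be blinded, and that participants are allocated at random to two groups.

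**Outcome.** The primary scale in section 2.4.1 has six items: colour, height, hardness, itching, pain and tightness. Each has a top score of 3. The efficacy index is the percentage fall in the total score from before to after treatment. Section 2.4 adds: "Assess fatigue marks once a week and save case photos".

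**The concern.** A mask protects a comparison only if it hides the thing that differs between the compared units. In the design of section 2.3 every patient has a blank scar, an A scar and a B scar. The subject's group then does not vary, and not knowing it leaves the evaluator free to know which scar is which. No sentence in the article says that the scar's condition is concealed.

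This matters because patients are openly unblinded, so the symptom items are exposed to expectation whatever is done. Masked rating of the signs is the only protection left for the primary score. Colour and hardness rest on verbal anchors judged by eye and touch. Height is banded in millimetres and leaves less room for judgement. If the evaluator can tell the blank scar from the treated ones, the rated signs may lean toward treatment, and a later report of blinded evaluation would not be supported by the protocol.

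**Working it through.** **Step 1. Compare the level of the mask with the level of the conditions.**

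| Place in the protocol article | Unit described |
|---|---|
| Abstract, methods | Scar within patient (blank control) |
| 2.2.2 Inclusion criteria | At least three scars per patient |
| 2.3 Interventions | Three scar areas per patient: blank, A, B |
| 2.5 Sample size | 60 patients in each group |
| 2.6 Allocation | Participants, two groups |
| 2.6 Mask | The subject's group |

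The first three rows describe a within-patient design, and the last three a comparison of patients. Two groups of 60 make 2 × 60 = 120, the number of patients in the abstract, so the two-group description is consistent in itself. A subject-level mask works under the two-group description and has no content under the self-controlled one.

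**Step 2. Share of the primary score at risk** (section 2.4.1).
- Maximum total: 6 items × 3 points = 18.
- Sign items (colour, height, hardness): 3 × 3 = 9, and 9/18 = 50%.
- Colour and hardness alone, the items most open to judgement: 2 × 3 = 6, and 6/18 = 33%.
- Symptom items (itching, pain, tightness): 9 points, reported by unblinded patients and exposed in any case.

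The article does not say who rates each item. The split into signs and symptoms is inferred from what the items measure.

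**Step 3. Illustration of size.** The index is (before − after)/before × 100%. If expectation lowers the after-treatment total of a treated scar by *b* points, the index rises by *b*/*T* × 100 percentage points, where *T* is the baseline total. The article gives no expected baseline, so *T* is an assumption.

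| Assumed baseline total *T* | *b* = 1 | *b* = 2 |
|---|---|---|
| 6 | 1/6 = 16.7 | 2/6 = 33.3 |
| 9 | 1/9 = 11.1 | 2/9 = 22.2 |
| 12 | 1/12 = 8.3 | 2/12 = 16.7 |
| 15 | 1/15 = 6.7 | 2/15 = 13.3 |

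These figures show how sensitive the index is to one or two rating points. They do not estimate a bias. Section 2.4.2 uses a 30% fall as the lower limit for an effect, but it refers to syndrome scores and does not say that these are the total from section 2.4.1. The comparison with 30% is therefore only a rough guide.

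**The case against.** **Section 2.6 has its own design.** It allocates participants to two groups, and within that description a mask on the subject's group is coherent. The deeper fault is then the unresolved unit of allocation. This stands, and it sets the order of the repair. Condition B includes an oral decoction, which the whole patient takes, so reconciliation could move A versus B to patient level. A mask on the patient's group would then have meaning for that comparison, while blank versus treated would still need a mask by scar.

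**The wording may be loose.** Section 2.3 uses control group, group A and group B as labels for scars, so a scar-level mask may have been intended. That is possible. Section 2.6 nevertheless names subjects, and the repair is the same: say scars.

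**Articles condense.** Order of assessment, coding of photographs and removal of gel residue are commonly left to a full protocol, and their absence is not the point here. The point is a stated safeguard placed at a level where it cannot work under the stated design.

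**Stronger readings.** A reader might infer that the evaluator sees the three scars side by side, must question the patient scar by scar, or can see which scar had gel. The article states none of this. A reader might also infer that knowing the visit favours treated scars. It applies equally to blank, A and B, so by itself it does not. Nor does the article say that the saved photographs go unused; it says only that they are kept.

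**Conclusion.** The point holds as a fault in the stated mask. Under the self-controlled design, section 2.6 does not conceal which scar is blank or treated, and 9 of the 18 primary points have no stated protection from rater expectation. The exposure falls chiefly on treated versus blank scars. A and B both receive the external medicine, so appearance separates them less, and that contrast is exposed mainly through the unblinded patient.

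The conclusion rests on section 2.3 governing the design, which the abstract and the inclusion criterion support and sections 2.5 and 2.6 contradict. It would be tempting to conclude that the evaluator will in fact be unmasked, or that the result will be biased by some number of points. The document supports neither. The range of 6.7 to 16.7 percentage points per rating point is an illustration at assumed baseline totals of 15 to 6. The repair also leaves the symptom half of the score exposed, so the gain is real but partial. The change should be made before recruitment, which section 2.9 says has not started.

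**What to change.** 1. Reconcile sections 2.3, 2.5 and 2.6 on the unit of allocation.
2. If the self-controlled design stands, reword section 2.6: the evaluator takes no part in treatment and is masked to which scar is blank, A or B. Scars are identified by a location code. No gel residue is visible at assessment, and this is arranged in a way consistent with the no-intervention rule for the blank scar in section 2.3.
3. Fix the order of assessment. The evaluator scores colour, height and hardness before any symptom question is asked. The patient then completes itching, pain and tightness on a form.
4. Keep colour rated in person, because one of its anchors depends on pressing the scar and cannot be read from an ordinary photograph. The saved photographs, coded and shuffled across scars and visits, may serve as a supportive check only.
5. If scar-level masking cannot be kept, do not describe the evaluation as blinded.

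The cost is a reworded section, a fixed order of assessment and a little evaluator time. The photographs are already planned. The evaluator must be kept apart from treatment, and the article does not say who applies the gel, so this should be confirmed locally.

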#### Primary outcome measures

2.4.1

We will use the international scar evaluation method—“*Vancouver Scar Evaluation Scale*” as the main standard for evaluating the efficacy.

1.Color: 3 points for bright red, 2 points for light red, and disappear after pressing, 1 point for non-red or some gray, 0 points for normal skin color;2.Height of scar marks: 3 points above 9 mm, 5 mm < 2 points for height ≤9 mm, 1 point for 1 to 5 mm, 0 points for flat or slightly depressed;3.Hardness: 3 points for hard as cartilage, 2 points for hardness like rubber, 1 point for softness, normal for softness skin score: 0 points;4.Itching: 3 points for severe or persistent itching, 2 points for frequent and tolerable itching, sometimes 1 point for itching, and 0 points for no itching;5.Pain: very intense 3 points for the “hyperalgesia,” 2 points for moderate-intensity allergic pain, sometimes 1 point for pain, and 0 points for no pain;6.tightness: 3 points for strong tightness, not too tight strong and tolerable score 2 points, slight tightness score, no tightness score 0 points.

Efficacy index = (total score before treatment − total score after treatment)/total score before treatment × 100%.

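### Evaluator blinding cannot reach the patient-reported items of the primary scar score (6, very probably 9, of its 18 points), so it does not protect the total

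*Protocol article*

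**What the plan says.** Section 2.4.1 of the protocol article adopts a scar scale "as the main standard for evaluating the efficacy". It lists six items, each with a top grade of 3. Three are signs that an examiner can see, measure or feel: "Color: 3 points for bright red, 2 points for light red"; "Height of scar marks: 3 points above 9 mm"; "Hardness: 3 points for hard as cartilage, 2 points for hardness like rubber". The other three are itching, pain and tightness. Itching is graded by severity, frequency and tolerability: "Itching: 3 points for severe or persistent itching, 2 points for frequent and tolerable itching". The efficacy index is the percentage fall in the unweighted total from before to after treatment.

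Section 2.6 states that patients and treating staff cannot be blinded, but that "the evaluator and statistician will be blinded to which group the subjects evaluated will belong". Section 2.3 makes an untreated scar the control, with no placebo or sham. The active treatments are a gel on the scar, with or without an oral decoction.

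**The concern.** Blinding an evaluator guards against bias in what the evaluator judges. It does nothing for an answer that the evaluator merely records. A patient who knows that one scar received gel and another received nothing may expect the treated one to itch or hurt less, and may report accordingly. That expectation runs in the direction of the trial's hypothesis, and it enters the primary total with the same weight per point as a measured change in height.

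At stake is what a positive result would mean. With one pooled total, a reader cannot tell whether the scar changed, whether the patient's report changed, or both. The only protection against assessment bias that section 2.6 names would appear to cover the whole primary outcome when it covers part of it.

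**Working it through.** **The plan's own figure.** The article gives no figure for the share of symptom items. Its only computed figure is the sample size in section 2.5: 49 per group, raised to 60. That rests on 11 points of the Constant–Murley questionnaire, a different instrument, with no SD stated. It cannot be reproduced directly. Solving for the missing SD (two-sided 0.05, 95% power) gives 11 × √(49/2) / (1.960 + 1.645) ≈ 15.1 on that questionnaire. This says nothing about the spread of the scar score and plays no part below.

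**Share of the total that evaluator blinding cannot reach.** Inputs are the item maxima in section 2.4.1.

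| Item | Maximum | Source of the rating |
|---|---|---|
| Colour | 3 | examiner |
| Height | 3 | examiner |
| Hardness | 3 | examiner |
| Itching | 3 | patient |
| Pain | 3 | patient |
| Tightness | 3 | very probably patient |

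- Maximum total: 6 × 3 = 18.
- Itching and pain: 2 × 3 = 6, and 6/18 = 33%.
- With tightness: 3 × 3 = 9, and 9/18 = 50%.

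The article never says in words who supplies each item. For itching and pain the grades leave no other source. Tightness is graded in part by whether it can be tolerated, which also points to the patient, but less firmly.

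**What a reporting shift would do to the efficacy index.** This is an illustration only. Both the shift per item and the baseline total are assumptions, because the article gives neither. With a shift of *b* points on each of *k* symptom items and a baseline total *T*, the index moves by 100 × *k* × *b* / *T* percentage points. For *k* = 3:

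| Assumed shift per item | *T* = 6 | *T* = 12 | *T* = 18 |
|---|---|---|---|
| 0.25 | 12.5 | 6.2 | 4.2 |
| 0.5 | 25.0 | 12.5 | 8.3 |
| 1.0 | 50.0 | 25.0 | 16.7 |

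If only itching and pain are patient-reported (*k* = 2), each entry falls by a third. For example, 0.5 at *T* = 12 gives 100 × 2 × 0.5 / 12 = 8.3. The spread from about 4 to 50 points shows that the size of any bias cannot be fixed from the document.

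**Which comparison is exposed.** Treated versus untreated scars: the patient sees where the gel goes, so she knows. Combined versus western treatment alone depends on the unit of allocation, and sections 2.3 and 2.6 differ on that. If the three scars lie in one patient (section 2.3), both treated scars get the external medicine and the decoction is systemic, so the text gives her no local sign by which to tell them apart. If patients are allocated to groups (section 2.6), she knows whether she takes the decoction.

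**The case against.** Section 2.6 is open about the lack of patient blinding and never claims that a blinded evaluator protects symptom reports, so the sentence is not false. Evaluator blinding still does its work for colour, height and hardness. This stands: a reader might infer that the blinding is worthless for the primary outcome, and the document does not support that.

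A reader might also infer that exactly half of the score is exposed. That needs tightness to be patient-reported, which is very probable but not stated; the secure figure is one third.

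It is tempting to set an assumed bias of a point or so against the difference that the sample size can detect, and to conclude that bias alone could produce a positive trial. The document does not support this either. It gives no SD or baseline for the scar score, its sample size belongs to another questionnaire, and a detectable difference for two independent groups would not apply to scars compared within a patient.

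Nor can the bias be assumed to drive the combined-versus-western contrast, for the reason given in the working.

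Two remedies that suggest themselves also fail or go too far. The article does say "Assess fatigue marks once a week and save case photos", but rating colour from those photographs does not work, because the 2-point colour grade depends on whether redness fades on pressing, and no coding of the photographs is mentioned. Making any efficacy claim conditional on a positive observer-rated result is a debatable trade-off: section 2.2.1 counts itching and pain among the main manifestations of these scars, so symptom relief is a legitimate aim.

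Finally, an open-label symptom measure is a common limitation, and some detail may sit in the full protocol. But the pooled total is fixed in section 2.4.1 of this article, and how it is analysed and described remains open to change.

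**Conclusion.** The point holds within limits. Patients are unblinded, the control has no sham, and the primary total includes itching and pain (6 of 18 points, 33%) and very probably tightness (9 of 18, 50%). Evaluator blinding therefore protects the observer-rated signs but not the total or the efficacy index, most clearly when treated scars are compared with untreated ones. The conclusion rests on one inference, that these symptoms are rated from the patient's own account: near certain for itching and pain, strong for tightness. The direction of any bias is predictable, but its size is unknown. The document does not show that a positive total would be due to reporting bias, only that the planned total could not separate the two.

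**What to change.** - **Sections 2.4.1 and 2.7:** alongside the total, prespecify separate analyses of the observer-rated sub-score (colour, height, hardness; 0-9) and the patient-reported sub-score (itching, pain, tightness; 0-9). State that a positive total will be interpreted in light of the observer-rated result.
- **Assessment procedure:** have the blinded evaluator rate colour, height and hardness before any symptom question is asked, so that nothing the patient says in answer can influence those ratings.
- **Section 2.6:** state that evaluator blinding covers only the observer-rated items, and that the symptom items are open-label reports.

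The item scores are needed for the total anyway, so the cost is some wording, a fixed rating order and one extra table, with no new staff. Section 2.9 says that recruitment has not started, so the change can be made before any data exist. The drawback is that the observer-rated sub-score does not capture symptom relief, which is why both sub-scores should be reported with the total rather than one replacing it.
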